### Study design

The study protocol and the measurements are presented in Fig. 1. As stated above, after informed consent and preliminary screening of the participants who have performed the MMSE and found eligible for inclusion in the study will also provide their basic demographic details (height, weight, etc.), self-reports of ongoing medications, along with the AUDIT and MRI screening questionnaire. The recruited participants indicated for prosthodontic rehabilitation are randomly allocated to either the experimental or the control group (see Fig. 1). A randomization list (www.randomization.com) is prepared by a nonparticipating member in the study and the randomization code is allocated over email upon request from the examiners. Further, all tests will be conducted according to the study protocol and at every test occasion, the participants will conduct saliva samples, mixing ability test, NA, questionnaires (OHIP-14, HAD) together with optional MRI acquisitions.

**Fig. 1 Fig1:**
[figure not shown]
Overview of the study protocol

The oral rehabilitation of the experimental group will start immediately after the first NA (pre-test). The control group on the other hand will be pre-and post-tested with an interval of about 3 months before the onset of the prosthodontic rehabilitation procedure. The relatively short period between the pre-and post-tests for the control group is motivated by ethical considerations. It is not considered justifiable to deny prosthodontic rehabilitation to the control group any longer than 3 months. Therefore, it is likely that the time between pre-and post-test for the control group will be slightly shorter than for the experimental group. We aim to statistically control for time differences by including time between pre-and post-test as a covariate of interest in the model. Both the experimental and the control group will also perform the post-tests (see Table 2) on two occasions after the completion of the oral rehabilitation procedures (Fig. 1). The first post-test occasion is after at least 3 months and the second test is to be conducted at 1-year follow-up, approximate time needed to adapt to the new fixed prosthesis.

**Table 2 Tab2:** Outcome measures

	Variable	Method/test	Measurements
*Primary outcome variables*			
1	Neuropsychological assessments	Episodic memory	BVMT-R
*Secondary outcome variables*			
2	Chewing function	Two-color chewing gum mixing test	VOH scores
3	Oral health	Oral health impact profile (OHIP) 14	OHIP score
4	Stress	Salivary test Hospital and anxiety depression scale questionnaire	Salivary Cortisol HAD score
5	Dentition status	Dental records, photos and X-rays	Eichner’s index Number of teeth Number of occluding units
6	Brain scans	Magnetic Resonance Imaging	Volume change hippocampus and/or total volume change gray matter

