### Intervention: oral rehabilitation

Individual treatment options will be discussed with the patients and rehabilitation will be provided depending on the clinical situation and the patient’s financial status. The rehabilitation will include fixed prosthodontics and will be achieved by providing the latest and most effective measures in modern-day prosthodontics. Briefly, the procedures will involve a control phase involving scaling, root planning, oral hygiene instructions, etc. When needed, extractions and bone augmentation will be performed, and also temporary removable dentures will be made if required. This will be followed by the restoration of the vertical dimension with occlusal splints (if needed), tooth preparations, placement of dental implants (if needed), and finally cementation of dental crowns. The entire rehabilitation phase is estimated to take approximately 3–12 months, where implant treatment is the main factor for the longer time frames.

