### Statistical methods

The data from the study will be entered in a Microsoft Excel sheet and exported to statistical software packages like SPSS Inc, Statistica, StatSoft Inc, or similar advanced analytics software packages for analysis. The result from the cognitive testing will be analyzed as repeated measure Analysis of covariance (ANCOVAs) with groups (experimental and control) and time (pre-and post-rehabilitation) as factors. Group-by-time interaction, the main effect of the group, and the main effect of time will be evaluated. To compare the magnitude of gains, the effect size (partial eta-square) will also be calculated. We will use time-length between pre-and post-tests as a covariate of interest with aiming to better control group differences. To predict the intervention outcomes, we will develop models that mainly predict cognitive test measures (NA). Predictive ability is defined as the amount of variance in the outcome that can be explained by pre-test cognitive status (slope method). Explained variance in the outcome will be obtained by analyzing linear regressions.

Preprocessing and statistical analyses of MRI data will be performed with Statistical Parametric Mapping (SPM) run in MATLAB (MathWorks). Movement correction will be performed by realigning and unwarp to the first image in the series. To consider group-specific anatomical brain differences, all patients will be normalized to Montreal Neurological Institute (MNI) echoplanar-imaging template. However, cortical thickness measures will not be normalized but rather used in their raw form. For cortical segmentation, a Freesurfer pipeline will be applied to the MRI images to produce regional cortical thickness and volumetric measures. To investigate rehabilitating-related changes repeated measures ANCOVAs will be performed with the groups (experimental and control) and time (pre-and post-rehabilitation) as factors. We will control for multiple comparisons with the Bonferroni-Holm method since all cognitive tests are correlated and because a majority of the test variables in this study belong to the same family (cognitive domain) or even the same test. In case of significant behavioral effects (i.e., a significant group-by-time interaction effect indicating that: the experimental group improves their cognitive performances > the control group), the changes will be evaluated as covariates of interest in relation to the potential brain changes.

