The study follows a clinical, longitudinal randomized trial design and has considered any possible bias due to type 1 error. Accordingly, the two pre-tests in the control group are included to rule out for test–retest effects of the cognitive measurements. The likelihood of the participants performing better in the cognitive tests in the second assessment is quite high. Therefore, the post-test in the control group will rule out any type 1 error due to an improvement over time that could potentially be interpreted as an improvement due to the intervention (dental rehabilitation). We hypothesize that at post-test (after the intervention), the experimental group will perform better in cognitive tests than the control group at post-test (i.e., the intervention improves the cognitive abilities better than what the test–retest effect does). However, at post-test 2 (after the intervention), we hypothesize that the control group will perform at a similar level as the experimental group as a result of gained effects due to the intervention. Importantly, the control group will probably have a shorter time length between pre-and post-test than the experimental group. This is a limitation that might lead to a greater risk of type- 2 errors and thereby decrease the possibilities to detect intervention effects. However, due to ethical reasons, we cannot deny the control group their dental rehabilitation any longer than 3–4 months after the pre-tests (see the method section for further information on the control for time differences between pre-and post-test). In contrast, if we detect positive intervention effects, we will be able to draw firm conclusions (i.e., despite a shorter time between pre-and post-test for the control group). Importantly, we will also evaluate if we can identify pre-intervention predictors for intervention outcomes. This is especially important regarding cognitive status (assessed with the pre-intervention neuropsychological tests) and we will therefore statistically model cognitive performances to predict intervention outcomes.

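### The pre-post interval does not overlap between arms (about 3–4 versus 6–15 months or more), so adjusting the group-by-time test for it is an extrapolation, with a loss of precision that depends on the unstated interval distribution

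*Protocol article*

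**What the plan says.** All references are to the protocol article.

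- **Control interval.** Study design has the control arm "pre-and post-tested with an interval of about 3 months before the onset of the prosthodontic rehabilitation procedure". The Discussion gives the limit as "we cannot deny the control group their dental rehabilitation any longer than 3–4 months after the pre-tests".
- **Experimental interval.** Under Study design, rehabilitation starts directly after the pre-test. Under Intervention: "The entire rehabilitation phase is estimated to take approximately 3–12 months, where implant treatment is the main factor for the longer time frames". Both post-tests follow completion of rehabilitation, and "The first post-test occasion is after at least 3 months".
- **Description of the difference.** Study design states that "it is likely that the time between pre-and post-test for the control group will be slightly shorter than for the experimental group".
- **Remedy.** Study design commits to the covariate: "We aim to statistically control for time differences by including time between pre-and post-test as a covariate of interest in the model". Statistical methods repeats it for the repeated-measures ANCOVA with group and time as factors: "We will use time-length between pre-and post-tests as a covariate of interest with aiming to better control group differences".
- **Interpretation.** The Discussion names the shorter control interval as a limitation that raises the type 2 error risk, and refers back to the covariate. It then says that "if we detect positive intervention effects, we will be able to draw firm conclusions", because the control interval is the shorter one.

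**The concern.** Covariate adjustment can separate elapsed time from arm only where the arms share some values of elapsed time. Here they share none. The model would have to predict how control participants would score at an interval none of them has, or how rehabilitated participants would score at an interval at which none of them is tested.

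The covariate is also not a baseline characteristic. In the experimental arm it is set by how long treatment takes, and the protocol says implant treatment is what mainly lengthens it. Adjusting for it can bring back the kind of confounding that randomisation removed.

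What is at stake is the group-by-time test on the primary outcome (BVMT-R) and the claim that a positive result would be firm. That claim treats the shorter control interval as working against a finding of benefit. The argument no longer applies once the interval has been regressed out.

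**Working it through.** **1. The plan's own figure.** Sample size gives 30 per group for partial eta-squared 0.06, α 0.05 and power 0.80. A two-group, two-occasion interaction calculation gives a total of 64 at a within-person correlation of 0 (power 0.777 at 60) and 58 at a correlation of 0.1 (power 0.818 at 60). The stated 60 is therefore approximately reproduced if the unstated correlation is about 0–0.1. The dropout step also reproduces: 30/(1 − 0.25) = 40. I take the plan's 80% as the starting point. Whether 0.06 should be read differently is a separate question and does not affect what follows.

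**2. Intervals.**
- Control: about 3 months, at most 3–4.
- Experimental minimum: 3 + 3 = 6 months.
- Experimental upper figure: 12 + 3 = 15 months, or more because the lag is at least 3 months.
- The control maximum (about 4) lies below the experimental minimum (about 6).

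**3. Precision.** Interval must interact with time if it is to adjust the group-by-time test. With two occasions, this equals regressing change on arm and interval. For equal arms:

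- R² of interval on arm = (gap/2)² / [(gap/2)² + mean within-arm variance]
- Variance inflation (VIF) = 1/(1 − R²)
- Power ≈ Φ[(1.960 + 0.842)/√VIF − 1.960]

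The protocol gives no distribution, so assume control uniform on 3–4 and experimental uniform on 6–15 months:

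- Means 3.5 and 10.5, so the gap is 7.0. Variances are 1/12 = 0.083 and 81/12 = 6.75, mean 3.417.
- R² = 12.25/(12.25 + 3.417) = 0.78.
- VIF = 4.6, so the standard error is multiplied by 2.14.
- Power = Φ(2.802/2.14 − 1.960) ≈ 0.26.
- A 4,000-run simulation with 30 per arm gave 78% power unadjusted and 26% adjusted.
- Restoring 80% would take about 30 × 4.585 ≈ 138 completers per arm.

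Other assumed experimental distributions, with control uniform on 3–4:

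| Experimental interval (months) | R² | VIF | Power |
|---|---|---|---|
| 80% at 6, 20% at 15 | 0.42 | 1.7 | 57% |
| 80% in 6–7, 20% in 14–15 | 0.50 | 2.0 | 51% |
| Half in 6–9, half in 12–15 | 0.71 | 3.5 | 32% |
| Uniform 6–18 | 0.75 | 4.0 | 29% |
| Uniform 6–15 | 0.78 | 4.6 | 26% |
| Right-skewed 6–15 | 0.78 | 4.6 | 26% |
| Triangular 6–15 | 0.88 | 8.1 | 17% |
| Uniform 6–9 | 0.91 | 10.6 | 14% |

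Two less natural shapes went higher: 14.7 when weighted towards 15 months, and 28 when everyone falls in 6–7 months, which does not fit a 3–12 month treatment phase. Changing the control distribution matters little. With experimental uniform on 6–15, VIF is 5.1 for control normal around 3 (SD 0.25) and 4.8 for control uniform on 2.5–4.

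**4. Source of the slope.** With uniform intervals, the experimental arm supplies 6.75/(6.75 + 0.083) = 99% of the within-arm information on interval.

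**5. Bias.** Adjusted effect = raw difference − slope × gap. With a 7-month gap, a slope of −0.05 SD per month moves the adjusted effect by +0.35 SD, and a slope of +0.05 moves it by −0.35 SD. These slopes are illustrations only; nothing in the protocol suggests a size or a sign.

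**6. Main effect only.** If interval enters without interval × time, power for group-by-time is not lost, but that contrast is not adjusted either.

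**The case against.** **The loss could be moderate.** The protocol's remark on implants points to a mixture of short and long courses, and mixtures give the lowest inflation in the table. With an 80/20 split, R² is about 0.5, which is far from a relabelling of arm. This stands. A reader might infer that most of the precision is certain to be lost, but the documents do not fix the interval distribution and so do not support that.

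**The exact model is not fixed.** The article says only that interval is a covariate, and detail may sit in an analysis plan. This stands in part. However, the stated purpose is to control the difference between groups, and only an interval × time term does that for the key test. The other specification leaves the purpose unmet.

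**Bias could run either way.** A reader might infer that the adjustment manufactures benefit. That needs a negative slope caused by treatment type. With the opposite sign the bias goes against benefit. If the slope were ordinary decline over time, the covariate would be correcting the contrast rather than distorting it. The data cannot tell these apart, so what can be defended is that the two are not separable.

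**The limitation is already admitted.** The Discussion does concede the unequal interval and the type 2 error risk. It does not recognise the lack of overlap, and it offers this same covariate as the remedy.

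**A richer model might rescue it.** A reader might expect a mixed model over all visits to identify the time slope, because control visits after rehabilitation overlap in time with experimental visits. All those overlapping visits are rehabilitated. No unrehabilitated visit exists beyond about 4 months in either arm, so the untreated slope at 6–15 months remains an extrapolation.

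**Conclusion.** The point holds. The lack of overlap is arithmetic from the protocol's text, and calling the control interval only slightly shorter contradicts the stated durations. Used as an adjustment of group-by-time, the covariate makes the primary contrast depend on a linear slope learned almost entirely in one arm, from a variable that arises after randomisation and is tied to implant treatment. Elapsed time and treatment type cannot be separated, and the adjusted effect may be biased in either direction.

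The precision cost is conditional on the assumed distribution and on an interval × time term. No definite power figure and no inflated false-positive rate follows from the documents. The timing is read from the text; Fig. 1 was not available for this check.

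**What to change.** - Remove the interval covariate from the primary model.
- Take as primary the group-by-time contrast without interval adjustment, using the experimental arm's first post-test and the control arm's retest before rehabilitation. Describe it as rehabilitation assessed at about 6–15 months or more versus a wait of about 3–4 months.
- In Study design, replace the statement that the control interval is only slightly shorter with the actual figures, and reconcile it with the Intervention section and the Discussion.
- Report any interval-adjusted model only as a sensitivity analysis, with its terms stated, and label it an extrapolation because no unrehabilitated visit exists beyond about 4 months.
- Tie the Discussion's claim of firm conclusions to the analysis without interval adjustment, and say that elapsed time remains part of that contrast.

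The cost is a change of wording and one relabelled analysis, with no change to visits or treatment. The small downside is that the primary contrast openly carries the interval difference, which the protocol already argues is conservative.

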**Methods:**

Eighty patients indicated for prosthodontic rehabilitation will be randomly assigned to an experimental or a control group. Participants will conduct neuropsychological assessments, masticatory performance tests, saliva tests, optional magnetic resonance imaging, and answer questionnaires on oral health impact profiles and hospital anxiety and depression scale before, 3 months, and 1 year after oral rehabilitation. The difference between the two groups is that the control group will be tested an additional time, (at an interval of about 3 months) before the onset of the oral rehabilitation procedure. The primary outcome is a change in measures of episodic memory performance.

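### The experimental post-test waits for completed rehabilitation while the control post-test runs on the calendar, so the first post-test contrast compares experimental completers with all controls who attend at 3 months

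*Protocol article*

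**What the plan says.** **Control group.** Protocol article, Study design (text after Fig. 1): "The control group on the other hand will be pre-and post-tested with an interval of about 3 months before the onset" of rehabilitation. This test is set by the calendar and does not depend on treatment.

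**Experimental group.** The same paragraph starts rehabilitation directly after the pre-test. The only post-tests it describes for this group are those that both groups "will also perform the post-tests (see Table 2) on two occasions after the completion of the oral rehabilitation procedures". Their timing is: "The first post-test occasion is after at least 3 months and the second test is to be conducted at 1-year follow-up". No latest date is given. The Abstract uses the same anchor, with tests "before, 3 months, and 1 year after oral rehabilitation".

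**Length and content of treatment.** Intervention: oral rehabilitation states: "The entire rehabilitation phase is estimated to take approximately 3–12 months, where implant treatment is the main factor for the longer time frames". It also says that "rehabilitation will be provided depending on the clinical situation and the patient’s financial status".

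**Analysis.** Statistical methods specifies a repeated-measures ANCOVA with group and time as factors, where time means before and after rehabilitation, and with the pre-to-post interval as a covariate. The Discussion states the main hypothesis as the experimental group's post-intervention test against the control group's post-test. By post-test 2 the controls have also been rehabilitated. The first post-test is therefore the only randomised contrast of treated with untreated participants.

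**The concern.** Whether a first post-test exists depends on a post-randomisation event, the completion of treatment, and it does so in one group only. A control gives a comparator score by attending at about 3 months. An experimental participant gives one only by finishing rehabilitation and then attending at least 3 months later.

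Under the written rule, someone who stops or never finishes has no test to attend, even if still willing. Someone whose treatment is prolonged is tested, but at no bounded time. If those who complete would have changed differently on the Brief Visuospatial Memory Test-Revised from those who do not, the group-by-time interaction picks up that difference along with any treatment effect.

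The planned covariate adjusts for interval length among people who have both scores. It cannot stand in for scores that the schedule never collects, and neither can a later analysis plan.

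The point also bears on the Discussion, which says that a positive result would permit firm conclusions despite the shorter control interval. That argument considers only the difference in intervals, not who reaches the experimental post-test.

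**Working it through.** **1. What each group must do to contribute a first post-test** (Study design; Intervention: oral rehabilitation)

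| | Control | Experimental |
|---|---|---|
| Trigger | about 3 months from pre-test | completion plus at least 3 months |
| Earliest time from pre-test | about 3 months | 3 + 3 = 6 to 12 + 3 = 15 months, by length of treatment |
| Latest time | about 3 months | none stated |
| Treatment must be finished | no | yes |

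**2. The plan's own figures** (Sample size)

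- Dropout: 30/(1 − 0.25) = 40 per group, which reproduces the enrolled number. The 20–25% is one rate for both groups and is not a non-completion rate for the experimental group.
- Effect size: partial eta squared 0.06 gives f² = 0.06/0.94 = 0.0638, f = 0.253 and d = 2f = 0.505.
- The 30 per group is approximately reproduced for a 2 × 2 within-between interaction only with a low pre-post correlation, which is not stated: 32 per group at a correlation of 0 and 29 at 0.1.
- If 0.06 is read directly as the interaction's partial eta squared, the total needed is 126–128.

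**3. Size of the shift.** Let q be the share of the experimental group without a post-test. Let D be the completers' mean change minus the mean change that the others would have shown, in SD of change.

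- Mean of the whole group = (1 − q) × completers' mean + q × non-completers' mean.
- Completers' mean − whole-group mean = q × D.

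The documents give neither q nor D. Assumed values are q = 0.10–0.25 (4–10 of 40 participants) and D = 0.3–0.5:

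- low: 0.10 × 0.3 = 0.03 SD
- high: 0.25 × 0.5 = 0.125 SD
- D = 0: no shift
- D negative: same size, against treatment

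**4. Against the planned effect**

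- With d = 0.505: 0.03/0.505 = 6% to 0.125/0.505 = 25%.
- With the difference in change that 30 per group detects at 80% power, 2.8 × √(2/30) = 0.72 SD: 0.03/0.72 = 4% to 0.125/0.72 = 17%.

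**5. Effect on the false-positive rate.** Assume no true effect, 40 controls tested, 40(1 − q) experimental participants tested, two-sided 0.05 and a normal approximation.

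- q = 0.10, D = 0.3: SE = √(1/36 + 1/40) = 0.230; 0.03/0.230 = 0.13; rejection probability about 5.2%.
- q = 0.25, D = 0.5: SE = √(1/30 + 1/40) = 0.242; 0.125/0.242 = 0.52; about 8.1%.
- A wider assumption, q = 0.20 with D = 1.0, gives a shift of 0.20 SD and about 13.5%.

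**The case against.** **The article nowhere says that unfinished participants go untested.** That is correct. It follows from the stated trigger. Fig. 1 is not shown, and the full protocol may hold a rule for people who stop. If it does, the point is met by stating that rule. But the article does fix a visit rule, and that rule makes every experimental post-test conditional on completion.

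**Prolonged treatment does not mean no test.** This stands. Such a participant is tested late rather than never. Only those who stop or never finish have no test.

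**A reader might infer that completion depends on money.** The Intervention section ties clinical situation and finances to the treatment given, not to whether it is finished. The Discussion adds that overdentures are allowed partly because of anatomical or economic limits and partly to retain more participants to post-tests. That should reduce such losses, but it does not provide a test for someone who still does not finish.

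**A reader might infer that the bias favours treatment.** The documents do not support a direction. Differences in level are largely removed by the pre-test, so only differences in change matter. Study participants says that people nearer mild impairment have more potential to improve. If they are the ones who do not complete, the bias would run against treatment.

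**A reader might take the Discussion to say that only type 2 error is possible.** It does not. It says the shorter control interval may raise that risk, and its remark about firm conclusions addresses the same issue.

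**Testing unfinished participants answers a different question.** In part it does: the contrast becomes one of being offered rehabilitation rather than of restored function. That is why a completers' analysis is kept as support.

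**Conclusion.** The concern holds as a possible selection bias built into the visit schedule. As written, the only randomised treated-versus-untreated contrast compares experimental completers with all controls who attend the 3-month visit. Controls can also drop out, so it is not a comparison with all controls as randomised.

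Size and direction are not determined by the documents. On the assumed 10–25% non-completion and 0.3–0.5 SD difference, the experimental mean shifts by 0.03–0.125 SD of change. That is 4–25% of the planned effect, depending on how the effect size is read, with a false-positive rate of about 5–8%. If completion is unrelated to cognitive change, there is no bias.

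On these assumptions the effect is modest, but missed tests cannot be recovered afterwards, so the schedule is worth changing. Until then, the Discussion's statement about firm conclusions needs qualifying for selection as well as for interval length.

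**What to change.** Change the assessment schedule only, not treatment:

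- Keep the first post-test at 3 or more months after completion for those who complete.
- Add a backstop date counted from the pre-test, for example about 15 months (the protocol's own 12 + 3). Any experimental participant who has by then stopped or not finished rehabilitation is given the planned test at that date.
- A participant who finished shortly before the backstop keeps the test at 3 or more months after completion, so the adaptation period is respected.
- Analyse all tested participants in the group to which they were randomised. Record completion status at the test, and report completers only as a supportive analysis.
- In the Discussion, state that the reading of a positive result also depends on who reached the experimental post-test.

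The cost is a schedule amendment and keeping contact with people who stop treatment: 4–10 of 40 under the assumed range. The test occasion is already planned. The statistical price is a slight dilution of the effect, because some participants are tested without finished rehabilitation.
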